**Enrolment**										
**Eligibility screen**	X									
**Informed consent**	X									
**Allocation**		X								
**Interventions**										
***IPTp-SP***			X	X	X	X	X	X		
***ISTp***			X	X	X	X	X	X		
**Assessments**										
***Mother***										
***Temperature***		X	X	X	X	X	X	X		
***Thick smear***		X	X	X	X	X	X	X		
***TDR, US-TDR***		X	X	X	X	X	X	X		
***Hb***		X	X	X	X	X	X	X		
***Mother***										
***Temperature***			X	X	X	X	X	X	X	
***Thick smear***			X	X	X	X	X	X	X	
***TDR, US-TDR***			X	X	X	X	X	X	X	
***Hb***			X	X	X	X	X	X	X	
***Offspring***										
***Weight, temperature***									X	
***APGAR***									X	
***Thick smear***									X	
***Hb***									X	
***Newborn assessment***										X

### Sample size {14}

The calculation of the sample size has performed using the Sealed Envelope Ltd. 2012. Power calculator for binary outcome non-inferiority trial. [Online] Available from: https://www.sealedenvelope.com/power/binary-noninferior/.

Referring to the results of a study comparing IPTp-SP and IST (dihydroartemisinin-piperaquine) [11], the number of participants required to detect a difference of 10% with a significance level of 5% and a power of 80% to assess the non-inferiority of IST to IPTp-SP vary as described in Table 2. Variables of interest considered were the malaria status, the anemia status, and the low birth weight rate.

**Table 2 Tab2:** Variation of the sample size according to the difference of the outcome of interest

	IPTp	IST	Sample size
Low birth weight	10.5	15.7	122
Malaria infection	18.9	23.4	196
Anemia	30	25	220

*NB*: IST with dihydroartemisinin-piperaquine and standard RDT was used as an example to calculate the sample size for the current study as there are no previous studies could be found that include assessment of Pyramax® and us-RDT for use as IST.

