### Trial design {8}

This is a 2-arm randomized (1:1 ratio) non-inferiority trial. A unique registration number will be associated with a randomization list number, generated before the start of the study and which will determine the assignment of study participants to one of the study arms.

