#### Outcomes {12}

##### Primary outcome

The primary outcome will be the assessment of the malaria status over the pregnancy at every visit for each study participant.

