### Recruitment {15}

Based on the assumption described above, a total of two hundred and twenty pregnant women is the minimal sample size required to answer our research question. However, anticipating on a non-compliance and/or loss-to-follow-up rate of 10%, the adjusted total sample size required will be 242 pregnant women (121 participants per arm).

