## Trial status

Date of beginning: 6 May 2021

Recruitment has already been completed, but the submission is done before the last patient/last visit. The submission was not done earlier because we were too immersed in the fieldwork and the exchanges with the co-authors took time because of the busy schedule of each of them.

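### Table 2 counts higher malaria and low-birth-weight rates in favour of IST, so the claimed 80% power is about 26% for malaria, the primary outcome, and 28% for low birth weight

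*Protocol article*

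**What the plan says.** The Trial design section states: "This is a 2-arm randomized (1:1 ratio) non-inferiority trial". The Sample size section names its tool as a "Power calculator for binary outcome non-inferiority trial" and presents "the number of participants required to detect a difference of 10% with a significance level of 5% and a power of 80" (per cent). It does not say whether the 5% is one-sided or two-sided.

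Table 2 lists the IPTp rate, the IST rate and the sample size for three outcomes. Two of its rows read "Low birth weight 10.5 15.7 122" and "Malaria infection 18.9 23.4 196". The anaemia row has 30, 25 and 220. A note under the table says that the rates come from IST with a standard RDT and dihydroartemisinin-piperaquine, used as an example because no study of the present combination was found.

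The Recruitment section takes the largest of the three figures: "a total of two hundred and twenty pregnant women is the minimal sample size required to answer our research question". It adds 10% to reach 242 (121 per arm).

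The Primary outcome section defines the primary outcome as "the assessment of the malaria status over the pregnancy at every visit for each study participant". Anaemia is listed under the secondary outcomes. The Objectives sections ask that malaria, anaemia and fetal morbidity be no more frequent with ISTp-US-Py, so a higher proportion is worse for every row of Table 2.

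**The concern.** When the outcome is a harm and the new strategy is assumed to be somewhat worse, part of the margin is already used up and the sample size must exceed that for equal arms. Table 2 shows the opposite. For malaria, IST is assumed to be 4.5 points worse, yet 196 women are said to suffice, whereas equal rates of 18.9% would need 380 by the same method. Low birth weight has the same fault.

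The power claimed for the primary outcome is at stake. The results are intended for the National Malaria Control Program's prevention policy (Dissemination plans). A reader who believes the trial had 80% power may take a failure to show non-inferiority on malaria as evidence against ISTp, when under the plan's own rates that failure is the most likely result.

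**Working it through.** **Inputs**

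- Margin 10 points, significance 5%, power 80%, and the rates: Sample size section and Table 2.
- 220 evaluable women (110 per arm), 242 enrolled (121 per arm): Recruitment section.
- Two-sided 95% confidence intervals for all statistics: General analysis principles. For non-inferiority this corresponds to a one-sided 2.5% level.
- The one-sided 5% level used below is inferred, because it reproduces the printed totals and one-sided 2.5% does not.

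**Formulas**

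n per arm = (z₁₋α + z₀.₈₀)² × [pC(1−pC) + pE(1−pE)] / d², with d the distance from the assumed difference to the margin. At one-sided 5%, (1.645 + 0.842)² ≈ 6.183. For a harm, d = 0.10 − (pE − pC).

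Power = Φ(d/SE − z₁₋α), with SE = √{[pC(1−pC) + pE(1−pE)]/n}.

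**Step 1: reproduce the printed totals**

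| Outcome | Sum of variances | d needed | n per arm | Total | Printed |
|---|---|---|---|---|---|
| Low birth weight | 0.105×0.895 + 0.157×0.843 = 0.2263 | 0.152 = 0.10 + 0.052 | 60.6 → 61 | 122 | 122 |
| Malaria | 0.189×0.811 + 0.234×0.766 = 0.3325 | 0.145 = 0.10 + 0.045 | 97.8 → 98 | 196 | 196 |
| Anaemia | 0.30×0.70 + 0.25×0.75 = 0.3975 | 0.150 = 0.10 + 0.050 | 109.2 → 110 | 220 | 220 |

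All three match exactly. One-sided 2.5% gives 154, 250 and 278, which do not match.

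The anaemia row adds the 5 points because IST is assumed better, which is right for a harm. The other two rows add 5.2 and 4.5 points although IST is assumed worse. As labelled, the table therefore mixes two conventions.

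**Step 2: correct the sign**

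| Outcome | Correct d | n per arm | Total for 80% power | Total at one-sided 2.5% |
|---|---|---|---|---|
| Low birth weight | 0.10 − 0.052 = 0.048 | 607.3 → 608 | 1,216 | 1,544 |
| Malaria | 0.10 − 0.045 = 0.055 | 679.6 → 680 | 1,360 | 1,726 |
| Anaemia | 0.150 (unchanged) | 110 | 220 | 278 |

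**Step 3: power at the planned size**

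Malaria, 110 per arm: SE = √(0.3325/110) = 0.0550. One-sided 5%: Φ(0.055/0.0550 − 1.645) = 26.0%. With 1.96 in place of 1.645: 16.9%.

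Low birth weight, 110 per arm: SE = √(0.2263/110) = 0.0454. Φ(0.048/0.0454 − 1.645) = 27.9%; with 1.96, 18.4%.

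| Scenario | One-sided 5% | Two-sided 95% CI |
|---|---|---|
| Malaria, Table 2 rates, 110 per arm | 26.0% | 16.9% |
| Malaria, Table 2 rates, 121 per arm | 27.6% | 18.1% |
| Low birth weight, Table 2 rates, 110 per arm | 27.9% | 18.4% |
| Malaria, both arms 18.9%, 110 per arm | 60% | 47% |
| Malaria, both arms 30% (prevalence in Study setting), 110 per arm | 49% | 37% |
| Anaemia, Table 2 rates, 110 per arm | 80% | 70% |

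**The case against.** The strongest reply is that the cause is not proven. The formula is symmetric in the two variances, so 196 and 122 would also result if the direction was right and the IPTp and IST columns were swapped in those two rows. Malaria power at 110 per arm would then be 84% at a one-sided 5% level. Alternatively, one wrong convention may have been used throughout, with the anaemia row printed in reverse; the anaemia row would then be wrong too. Only the cited study could settle this, and it is not at hand. It follows that the rates should be checked against that source when the table is corrected. The finding stands, because nothing in the document supports a swap and no other section repairs the inconsistency.

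A second reply is that the rates are only an example, from a less sensitive test and another drug, and that ISTp-US-Py may do better. With 18.9% in the control arm, power at 110 per arm (one-sided 5%) is 74% if ISTp has 17% malaria and 81% if it has 16%. So 26% is one end of a range. However, the plan assumes no such advantage for malaria, and equal arms still fall well short of 80%.

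Two smaller points are fair. The calculation treats malaria as one yes/no result per woman, as the plan's own sample size does, while the outcome is assessed at every visit; the power figures belong to that planning model. The main objective also names anaemia beside malaria, and sizing on the largest row is not in itself a fault. The fault is that the malaria row is not truly covered by the 220.

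**Conclusion.** The point holds. As labelled, Table 2 reverses the sign for malaria and low birth weight. The required totals are 1,360 instead of 196 and 1,216 instead of 122. With 220 evaluable women, power is about 26% for malaria and 28% for low birth weight, or 17% and 18% under the planned 95% interval. The 220 reaches 80% only for anaemia, only if ISTp is 5 points better, and only at a one-sided 5% level.

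These figures rest on Table 2's rates as printed, the 10-point margin, the unpooled normal formula and one binary result per woman. The one-sided 5% level is inferred from the exact match of all three totals. The stricter level implied by the analysis section only lowers the power.

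**What to change.** - Check the rates and column labels of Table 2 against the cited study. With the rates as printed, correct the totals to 1,216 (low birth weight), 1,360 (malaria) and 220 (anaemia), and state that the level is one-sided 5%.
- Replace the statement that 220 women answer the research question with the achieved power for malaria: about 26% (one-sided 5%) or 17% (two-sided 95% interval) at the planning rates, and 60% or 47% if the arms are equal.
- State the three conditions under which 220 gives 80% power for anaemia.
- State before the results are known that a malaria confidence interval crossing the margin is inconclusive.

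The Trial status section says "Recruitment has already been completed, but the submission is done before the last patient/last visit", so no further enrolment is asked for, and on that timeline the correction could still precede the analysis. The cost is a text change in the sample-size section, carried into the report and into the analysis plan where it repeats these figures, and a much less favourable power statement.

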## Discussion

This protocol will assess the proportion of maternal malaria, maternal anemia, spontaneous abortions or intrauterine death during pregnancy, fetal morbidity, and neonatal mortality at childbirth in ISTp-US-Py compared to IPTp-SP. WHO recommends a package of interventions for preventing malaria and its adverse effects during pregnancy, which include the IPTp-SP as a prevention strategy to control malaria in sub-Saharan countries [5]. SP depends on the doses and ANC coverage, but in addition to that, the strategy is now threatened by the spread of *Plasmodium*-resistant strains. The resistance to SP undermines the ability of IPTp-SP to minimize the adverse effects of malaria in pregnancy [19], necessitating alternative approaches [20]. The potential approach is the ISTp which depends on the generation of the rapid diagnostic test and the ACT used. Moreover, the pooled analysis of five trials provides further evidence that ISTp with the current generation of RDTs is not superior to the existing strategy of IPTp with SP [21].

The us-RDT used in this trial has a higher sensitivity [22] than the conventional ones and the ACT used is newly approved as the antimalarial in DRC. The effective and safe treatment is needed to protect a pregnant woman with malaria, which is the objective of this project. At our knowledge, this study is the first to use the combined us-RDT in the ISTp strategy and Pyramax® as treatment. Pregnant women are a vulnerable population and require special attention. For that, the outcome of this study will be relevant in settings where malaria in pregnancy has a high morbidity and where the SP resistance is emerging. If successful, the findings can be the evidence-base for the update of malaria control policy by the NMCPs.

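### The 220 women that fix the trial size give 80% power for anaemia only if ISTp lowers it from 30% to 25% and the test is one-sided at 5%; with the planned two-sided 95% interval power is 70%, and with equal rates of 30% it is 49% or 37%

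*Protocol article*

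**What the plan says.** The Sample size section {14} used an online calculator described as a "Power calculator for binary outcome non-inferiority trial". It sets out "the number of participants required to detect a difference of 10% with a significance level of 5% and a power of 80" per cent. It does not say whether the 5% is one-sided or two-sided.

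Table 2 then gives three rows (IPTp rate, IST rate, total size):

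- "Low birth weight 10.5 15.7 122"
- "Malaria infection 18.9 23.4 196"
- "Anemia 30 25 220"

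A note below the table explains that "IST with dihydroartemisinin-piperaquine and standard RDT was used as an example to calculate the sample size for the current study". Recruitment {15} takes the anaemia figure forward: "a total of two hundred and twenty pregnant women is the minimal sample size required to answer our research question". It then adds 10% to reach 242, or 121 per arm.

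Three other places bear on this:

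- General analysis principles, under Statistical methods {20a}, makes all confidence intervals two-sided at the 95% level.
- The Outcomes section {12} makes malaria status the primary outcome and lists anaemia among the secondary ones, although the Main objective names both.
- The Discussion reports a pooled analysis of five trials in which "ISTp with the current generation of RDTs is not superior to the existing strategy of IPTp with SP".

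**The concern.** In the anaemia row IST is assumed to be truly 5 points better than IPTp. The distance from the assumed truth to the margin is therefore 15 points, not 10, and the stated 80% power depends on that assumed benefit. The text around the table speaks only of a 10% difference and does not say how much power remains if the two strategies are equally good, which is a natural case for a non-inferiority trial.

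The size was also computed at a one-sided 5% level, while the planned two-sided 95% interval corresponds to a one-sided 2.5% level. So the stated power is not reached even if the assumed rates are right.

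The results are meant to inform national policy. A reader who trusts the 80% could take a failure to show non-inferiority on anaemia as evidence against ISTp, when it may reflect only the size of the trial.

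**Working it through.** **Inputs.** Margin 10 points, significance 5%, power 80%, anaemia 30% on IPTp and 25% on IST (Sample size {14} and Table 2); 220 in total, so 110 per arm, and 121 per arm enrolled (Recruitment {15}); two-sided 95% intervals (Statistical methods {20a}). The 10% difference is read as the non-inferiority margin. Non-inferiority is taken to be shown when the upper confidence limit for IST minus IPTp lies below 10 points.

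**Formula.** With event rates p1 (IPTp) and p2 (IST) and distance d = 0.10 − (p2 − p1),

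n per arm = (z_alpha + z_beta)² × [p1(1−p1) + p2(1−p2)] / d²

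power = Φ(d/SE − z_alpha), where SE = √([p1(1−p1) + p2(1−p2)]/n).

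**Reproducing 220.** The variance sum is 0.30 × 0.70 + 0.25 × 0.75 = 0.3975, and d = 0.10 + 0.05 = 0.15.

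- One-sided 5%: (1.645 + 0.842)² = 6.18; 6.18 × 0.3975 / 0.0225 = 109.2, so 110 per arm and **220 in total**, as stated.
- One-sided 2.5%, which matches a two-sided 95% interval: 139 per arm, 278 in total.

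Other readings do not give 220. Entering 30 and 25 as success rates gives 1968. A superiority comparison of 30% with 25% gives 1972 (one-sided) or 2502 (two-sided).

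**Power at the assumed rates, 110 per arm.** SE = √(0.3975/110) = 0.0601; 0.15/0.0601 = 2.495.

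- One-sided 5%: Φ(2.495 − 1.645) = 80%.
- Two-sided 95% interval: Φ(2.495 − 1.960) = 70%.

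**Power at equal rates of 30%, 110 per arm.** The variance sum is 0.42, d = 0.10, SE = √(0.42/110) = 0.0618; 0.10/0.0618 = 1.618.

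- One-sided 5%: Φ(1.618 − 1.645) = 49%.
- Two-sided 95% interval: Φ(1.618 − 1.960) = 37%.

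Exact binomial calculation agrees: 49.1%, and 36.9% (Wald) or 37.6% (Newcombe).

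**Range.**

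| True anaemia rates, IPTp v IST | Per arm | One-sided 5% | Two-sided 95% interval |
|---|---|---|---|
| 30% v 25% | 110 | 80% | 70% |
| 30% v 30% | 110 | 49% | 37% |
| 25% v 25% | 110 | 53% | 40% |
| 30% v 25% | 121 | 83% | 74% |
| 30% v 30% | 121 | 52% | 40% |

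For 80% power at equal rates of 30%, the formula gives 6.18 × 0.42 / 0.01 = 259.7, so 260 per arm and 520 in total at one-sided 5%. With the two-sided 95% interval it gives 660 in total.

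**The other two rows.** 122 and 196 reproduce at one-sided 5% only if IST's higher rate is counted as a benefit, so that the distances are 15.2 and 14.5 points. With low birth weight and malaria treated as adverse outcomes, the distances are 10 − 5.2 = 4.8 and 10 − 4.5 = 5.5 points, and the totals become 1216 and 1360.

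**The case against.** A good deal can be said for the plan. Assuming a true difference in a non-inferiority calculation is legitimate, and sizing at equality is a common choice rather than a requirement. The 30 v 25 assumption is printed in Table 2, the note admits that a proxy regimen was used, and Recruitment refers back to the assumption. Nowhere does the article claim 80% power at equal rates. All of this stands: the 220 is correct arithmetic for its inputs.

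A reader might infer that the authors chose the one outcome on which IST is assumed to win. The documents do not support that. 220 is the largest figure in Table 2, and taking the largest is the usual cautious rule.

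A reader might also infer that the Discussion denies the assumed benefit. It does not. The sentence on the pooled analysis names no outcome and does not mention anaemia, and the Discussion goes on to set this trial's us-RDT apart as more sensitive. There is still some tension, because the rates in Table 2 also come from IST with a standard RDT.

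The objection does not remove the mismatch between the error level used for sizing and the planned interval, or the dependence of the stated power on the assumed benefit. Both follow from figures that the article itself gives, so neither is a matter left to an analysis plan that is not shown.

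**Conclusion.** The concern holds in this form. The trial size rests on a secondary outcome, and its 80% power needs both a true fall in anaemia from 30% to 25% and a one-sided 5% test. The planned interval gives 70% under those same rates. At equal rates of 30% the power is 49% or 37%, and using all 121 women per arm lifts this only to 52% or 40%. The assumed benefit has thin support: one study of IST with a standard RDT and a different ACT, and a Discussion that reports no superiority for ISTp with such tests.

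The conclusion rests on reading the 10% difference as the margin and on judging non-inferiority from the two-sided 95% interval that the article prescribes for all statistics. It does not show that the sample size was calculated wrongly for anaemia or that assuming a benefit was improper. It shows that the stated power, and the claim that 220 women suffice, are more favourable than the planned analysis delivers.

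**What to change.** In Sample size {14} and Recruitment {15}, replace the statement of power with wording such as:

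*With 110 women per arm and a 10-point margin, power for anaemia is 80% at a one-sided 5% level, or 70% with the planned two-sided 95% confidence interval, if the true rates are 30% (IPTp) and 25% (IST). If both rates are 30%, power is 49% and 37% respectively.*

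Delete the sentence in Recruitment that presents 220 as the minimum needed to answer the research question. Say that the anaemia rates come from IST with a standard RDT and that anaemia is a secondary outcome.

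The Trial status section reports recruitment as complete, and no change in enrolment is needed. The only cost is a less favourable stated power.

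The malaria and low birth weight rows need their own correction of direction. Restating the anaemia row alone would leave 196 and 122 standing.

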### Recruitment {15}

Based on the assumption described above, a total of two hundred and twenty pregnant women is the minimal sample size required to answer our research question. However, anticipating on a non-compliance and/or loss-to-follow-up rate of 10%, the adjusted total sample size required will be 242 pregnant women (121 participants per arm).

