### Objectives {7}

#### Main objective

The main objective of the study is to assess that the proportion of maternal malaria, maternal anemia, and their impact on the offspring is non-inferior when using ISTp-US-Py compared to IPTp-SP.

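### The 220 women are sized on single outcomes, so the stated 80% power does not hold for the joint main objective, and on Table 2's printed rates it does not hold for malaria, the primary outcome, either

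*Protocol article*

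**What the plan says.** The Main objective is to "assess that the proportion of maternal malaria, maternal anemia, and their impact on the offspring is non-inferior when using ISTp-US-Py compared to IPTp-SP". The hypothesis in Background and rationale {6a} and the text on the choice of comparators list the same outcomes, and more, joined by 'and'.

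The outcome sections differ. Outcomes {12} names malaria status over the pregnancy as the primary outcome. The outcome definitions under Statistical methods {20a} add parasite density to it. Both places list anemia and the fetal or neonatal outcomes as secondary.

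Sample size {14} uses a calculator for one binary outcome, with a 10% difference and "a power of 80% to assess the non-inferiority of IST to IPTp-SP vary as described in Table 2". It adds: "Variables of interest considered were the malaria status, the anemia status, and the low birth weight rate". Table 2 gives three totals:

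- low birth weight: IPTp 10.5%, IST 15.7%, total 122
- malaria infection: IPTp 18.9%, IST 23.4%, total 196
- anemia: IPTp 30%, IST 25%, total 220

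Recruitment {15} then states that "a total of two hundred and twenty pregnant women is the minimal sample size required to answer our research question", and adds 10% to reach 242 (121 per arm). General analysis principles sets all confidence intervals as two-sided 95%.

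**The concern.** The largest of three single-outcome sample sizes gives each outcome at least its nominal power when tested alone. It does not give that power for showing non-inferiority on all three. The number chosen is the anemia row, which is a secondary outcome, so the size matches neither the joint objective nor the stated primary outcome.

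The results are meant to inform national policy. If it is unclear which outcome decides, a result that meets the margin on anemia but not on malaria could be presented as support for the strategy. If all three must succeed, a strategy that truly performs as assumed could fail much more often than the one time in five that 80% implies.

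**Working it through.** **Inputs.** The rates and totals come from Table 2. The margin is 10 percentage points, power 80% and significance level 5% (sidedness not stated), all from Sample size {14}. Recruitment {15} gives 220 in total, so 110 per arm. General analysis principles gives two-sided 95% intervals, which for non-inferiority means one-sided 2.5%. The correlation between outcomes is not in the document; I assume a common value and show 0, 0.5 and 0.9.

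**Step 1: reproduce Table 2.** n per arm = (z₁₋α + z₀.₈)² × V / d², where V = p₁(1−p₁) + p₂(1−p₂) and d is the distance from the assumed difference to the margin. At one-sided 5%, (1.645 + 0.842)² = 6.18.

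- Low birth weight: V = 0.2263. With d = 0.10 + 0.052 = 0.152, n = 60.6, rounded up to 61; total 122.
- Malaria: V = 0.3325. With d = 0.10 + 0.045 = 0.145, n = 97.8, rounded up to 98; total 196.
- Anemia: V = 0.3975. With d = 0.10 + 0.05 = 0.15, n = 109.2, rounded up to 110; total 220.

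All three totals match. With the same distances, one-sided 2.5% gives 154, 250 and 278, which do not match.

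**Step 2: check the directions.** All three outcomes are adverse. For anemia, IST is assumed 5 points better, so 10 + 5 is right. For malaria and low birth weight, IST is assumed worse, by 4.5 and 5.2 points. The distance should then be 10 − 4.5 = 5.5 and 10 − 5.2 = 4.8 points. The values 14.5 and 15.2 arise only if infection and low birth weight are treated as favourable. In the correct direction, 80% power at one-sided 5% needs 1,360 in total for malaria and 1,216 for low birth weight.

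**Step 3: power per outcome at 110 per arm.** Power = Φ(d/SE − z₁₋α), with SE = √(V/110).

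| Outcome | SE | Table 2's implied direction, one-sided 5% | Correct direction, one-sided 5% | Correct direction, one-sided 2.5% |
|---|---|---|---|---|
| Low birth weight | 0.0454 | Φ(3.351 − 1.645) = 95.6% | Φ(1.058 − 1.645) = 27.9% | 18.4% |
| Malaria | 0.0550 | Φ(2.637 − 1.645) = 84.0% | Φ(1.000 − 1.645) = 26.0% | 16.9% |
| Anemia | 0.0601 | Φ(2.495 − 1.645) = 80.2% | 80.2% (unchanged) | 70.4% |

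**Step 4: joint power for all three.** Under independence this is the product, for example 0.956 × 0.840 × 0.802 = 0.644 and 0.279 × 0.260 × 0.802 = 0.058. Otherwise it is a trivariate normal probability with a common correlation.

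| Setting, 110 per arm | Correlation 0 | 0.5 | 0.9 |
|---|---|---|---|
| Table 2's implied directions, one-sided 5% | 64.4% | 70.5% | 77.2% |
| Correct direction, one-sided 5% | 5.8% | 13.1% | 20.9% |
| Correct direction, one-sided 2.5% | 2.2% | 7.0% | 13.0% |

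If all 121 per arm were analysed, the first row becomes 70.3%, 75.1% and 80.8%. The correct-direction row at one-sided 5% becomes 6.8%, 14.4% and 22.4%.

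**The case against.** The strongest objection is that the document has an outcome hierarchy. Malaria is primary, anemia and the offspring outcomes are secondary, and nothing requires all three to succeed. On that reading there is no joint test to power, and taking 220 rather than malaria's 196 looks cautious. The decision rule may also sit in the analysis plan, which is not shown.

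Part of this stands. A co-primary requirement is one reading of passages that disagree; it is not an established rule of the trial. It does not clear the plan, though. The objective, the primary outcome and the sizing are all printed here and do not fit together. The malaria-only reading does not rescue the 80% either, since on the printed rates malaria alone has 26% power.

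A reader might draw three stronger conclusions that the document does not support:

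- That 64–71% is the power on the plan's own inputs. It is not. Those figures carry over the reversed direction in two rows of Table 2. That reversal causes most of the shortfall; sizing the outcomes one at a time is the smaller part.
- That the false-claim rate is inflated because success on any one of the three outcomes would suffice. No section states such a rule.
- That the trial should be enlarged. Trial status reports that recruitment is complete.

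**Conclusion.** The point holds. The stated 80% power does not apply to the main objective as worded. At 110 per arm it falls short at every correlation examined, even if Table 2 is taken at face value (64–77%). Only with no losses at all, correlation 0.9 and the reversed directions does it just pass 80%.

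On the printed rates, read as adverse outcomes, joint power is about 6–21% at one-sided 5% and 2–13% at the level of the planned intervals. For malaria alone the figures are 26% and 17%.

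These results rest on a 10-point absolute margin, on the normal approximation that reproduces Table 2 and on an assumed common correlation. They also rest on Table 2's rates, which the protocol took from a different screening strategy (a standard RDT with dihydroartemisinin-piperaquine) for want of data on its own. If the ultrasensitive test and the study drug do better than those rates, power is higher; the document gives no figure for that.

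**What to change.** 1. In Background and rationale {6a} and the Main objective, state that malaria status over pregnancy, as in Outcomes {12}, alone decides non-inferiority. Make anemia and low birth weight secondary, with no confirmatory claim. Bring the comparator text into line, along with the parasite-density addition in the outcome definitions.
2. In Sample size {14} and Recruitment {15}, replace the 80% with the power that 220 women give for malaria on the printed rates, in the correct direction and at the level of the planned intervals: about 17%, or 26% at one-sided 5%.
3. If the joint objective is kept, state that every outcome must meet the margin, and give the joint power computed the same way with the assumed correlation shown.

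No extra enrolment is asked for, and the change should be made before the analysis. The cost is some rewording, the loss of any confirmatory claim on anemia or low birth weight, and a much less favourable stated power.

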## Statistical methods

### Statistical methods for primary and secondary outcomes {20a}

#### General analysis principles

Data analysis will be performed after the end of the follow-up period of the last participant included in the study.

Study participants will receive two different interventions depending on which group they are enrolled in. The first group will undergo intermittent screening during pregnancy using ultra-sensitive malaria rapid diagnostic test and treatment with pyronaridine-artesunate—Pyramax® (ISTp-US-Py), and the second group will receive an intermittent preventive treatment as suggested by the NMCP. The analysis will mainly compare the two groups to assess the outcomes of the study. All AEs (severe or non-severe) will be reported in the trial publication and compared in the study arms and gestational weeks. To assess the effect of the study interventions in the IPT and the ISTp arms, we will use the intention-to-treat approach. Meaning that all the participant who has been randomized to an arm or another will be considered as part of that arm for the analysis despite their level of completion.

Data from every woman included with baseline and at least one further visit will be analyzed in the treatment arms to which they were assigned. Safety data from all participants who received at least one dose of the study drug will be used in the analysis to describe AEs. AEs will be grouped by treatment group for the number of events and number of participants with type of event. Descriptive statistics will be summarized by treatment arm and visits.

For all statistics, the confidence intervals will be two-sided and at the 95% level, and the value of *p* < 0.05 will be interpreted as statistically significant.

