### Methods in analysis to handle protocol non-adherence and any statistical methods to handle missing data {20c}

For each variable, statistical tests will be performed with the available data. A 10% sample size adjustment will be made to ensure adequate power despite the loss to follow-up of some participants.

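### The 10% loss allowance is multiplied on (220 × 1.10 = 242) instead of divided out (220 / 0.90 = 244.4), so 242 protects the stated minimum of 220 only up to 9.1% without usable data

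*Protocol article*

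**What the plan says.** Sample size {14} sets out the calculation as the number of women needed "to detect a difference of 10% with a significance level of 5% and a power of 80" per cent, for three outcomes. The largest row of Table 2 is anemia: "Anemia 30 25 220". Recruitment {15} adopts it: "a total of two hundred and twenty pregnant women is the minimal sample size required to answer our research question". The same section then adds an allowance, "anticipating on a non-compliance and/or loss-to-follow-up rate of 10" per cent, and arrives at its enrolment figure: "the adjusted total sample size required will be 242 pregnant women (121 participants per arm").

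The section on non-adherence and missing data {20c} gives the purpose of the step: "A 10% sample size adjustment will be made to ensure adequate power despite the loss to follow-up of some participants".

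Two other sections bear on who is counted.

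- General analysis principles, under {20a}, specifies intention to treat regardless of how far a woman completed the study. It analyses women who have baseline data and at least one later visit.
- The retention section {18b} keeps data gathered before a woman is lost to follow-up, but discards the data of women who withdraw consent.

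**The concern.** An allowance for loss should be set so that the required number remains after the loss. The anticipated rate is a fraction of the women enrolled, so the enrolled number N must satisfy N × (1 − 0.10) ≥ 220. The protocol instead adds 10% of the required number, which always gives too small a total.

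At stake is whether the only stated enrolment figure does the job that {20c} assigns to it. If all of the anticipated 10% are lost to the analysis, 242 falls below the number that the same paragraph calls the minimum. The base figure has almost no slack, because 109.2 per arm was rounded up to 110. The allowance is therefore the only cushion.

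**Working it through.** **Inputs.** Minimum total 220, anticipated rate 10% and enrolment figure 242 (121 per arm) are from Recruitment {15}. Anemia at 30% under IPTp and 25% under IST, the 10-point margin, the 5% significance level and the 80% power are from Sample size {14} and Table 2. The 1:1 allocation is from Trial design {8}.

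**Step 1: reproduce the 220.** For non-inferiority of two proportions with unpooled variance, and anemia as a harmful event:

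n per arm = (z for alpha + z for power)² × [p1(1 − p1) + p2(1 − p2)] / (margin + benefit)²

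With one-sided 5% and 80% power: (1.645 + 0.842)² × (0.30 × 0.70 + 0.25 × 0.75) / (0.10 + 0.05)² = (1.645 + 0.842)² × 0.3975 / 0.0225 = 109.2. This rounds up to 110 per arm, or 220 in total, an exact match. With one-sided 2.5%, which corresponds to a two-sided 95% interval, the same formula gives 278. The 220 therefore rests on one-sided 5%, although Sample size {14} does not say so.

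**Step 2: reproduce the 242.** 220 × 1.10 = 242, also an exact match. The allowance was multiplied on.

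**Step 3: the allowance as a fraction of those enrolled.** 220 / (1 − 0.10) = 244.4, so 245, or 246 (123 per arm) for equal arms. Check: 246 × 0.90 = 221.4, which covers 220. The gap to 242 is 3 to 4 women.

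**Step 4: what 242 delivers.**

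- If the full 10% contribute nothing: 242 × 0.90 = 217.8, about 218 in total or 109 per arm. This is 2 below 220.
- Break-even: 242 − 220 = 22 women, and 22 / 242 = 9.1%. The minimum is kept as long as no more than 22 women lack usable data.

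**Step 5: effect on power.** For the anemia row, power = Φ[0.15 / √(0.3975 / n) − z for alpha].

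| Per arm | One-sided 5% | One-sided 2.5% |
|---|---|---|
| 110 | 80.2% | 70.4% |
| 109 | 79.9% | 70.0% |

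The loss step costs about 0.3 to 0.4 percentage points in either column. The choice of significance level costs about 10 points.

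**The case against.** The strongest reply is that the 10% is a rate of non-compliance and/or loss to follow-up, not a rate of removal from the analysis. Intention to treat keeps non-compliant women. The retention section {18b} keeps what was collected before loss. Anemia in pregnancy is assessed at every visit, so a woman lost late has already contributed. This stands. A reader might infer from 242 × 0.90 that the trial will have only 218 evaluable women and so misses its own requirement. The documents do not support that as a flat statement, since it needs all 10% to yield no usable data. Some removal is nonetheless real: women who withdraw consent are dropped, and those with no visit after baseline are not analysed. The protocol does not say what share of the 10% these groups make up.

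A second reply is size. Two women analysed, or 3 to 4 enrolled, change no decision, and 79.9% still rounds to the planned 80%. Allocation is by simple randomization, so the chance spread in arm size (SD about √(242 × 0.25) = 7.8) is larger than a deficit of 1 per arm. This also stands, and it limits the point to a minor correction.

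A third reply is that 220 belongs to anemia, listed as a secondary outcome, while the primary outcome is malaria status, for which Table 2 gives 196. Taken at face value, 218 exceeds 196. However, Recruitment {15} itself names 220 as the minimum, and that is the figure the allowance is meant to protect.

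**Conclusion.** The point holds as a small error in a stated figure: 242 does not follow from 220 and a 10% loss rate. The matching number is 244.4, or 246 with equal arms. In the worst case under the protocol's own rate, about 218 women remain, 2 short of the minimum, and anemia power is 79.9% instead of 80.2%. The shortfall disappears if no more than 22 women (9.1%) lack usable data, which the analysis rules make quite possible.

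The figures rest on the Table 2 anemia rates, a 10-point margin, one-sided 5% and equal arms.

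A reader might go further and infer that the trial is underpowered because of this step. It is not: the change is about 0.3 points. Nor does the step show that 220 was adequate to begin with. The analysis plan states that "the confidence intervals will be two-sided and at the 95% level", for which the same anemia calculation needs 278. That is a separate question, and correcting the loss allowance would not settle it.

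**What to change.** Trial status reports that recruitment has ended, so the enrolment figure should not be changed to 246. That could no longer affect the trial and would misreport what was planned. Instead, in Recruitment {15} and in {20c}:

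- State that 242 enrolled preserves 220 only if at most 22 women (9.1%) lack usable data, and that a full 10% without data leaves about 218, or about 109 per arm.
- Say whether the 10% means removal from the analysis or also covers women whose data are kept under intention to treat and the retention section {18b}.
- If power is restated, label it as applying to the anemia row at one-sided 5%. Do not present 79.9% as the trial's power under the two-sided 95% intervals.

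The cost is one or two sentences, with no change to conduct or analysis.
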